## **1.0 Purpose of the study:**

This study aims to develop and refine a survey instrument that evaluates consumer perception of a healthy label and the willingness to pay for it. The overall objectives of the project are to:

1. Understand and describe behaviorally segmented elasticity measures and estimates of the response to variations in nutrition-related food labeling.
2. Evaluate the impact of trust in various food-related institutions on food choice.
3. Evaluate the impact of a “healthy” food label, both with and without FDA endorsement, on snack food choices.
4. Identify nutrition-related food label components best suited for policy and regulatory updates aimed at improving the healthfulness of snack food choices.

This project is divided into two Phases. The primary objective of Phase 1 of this project is to pre-test the survey tool to refine and improve the presented content. Data collected from Phase 1 will not be retained or used for further analysis beyond the improvement of the survey for Phase 2. Phase 2 will proceed only after protocol modifications are submitted to incorporate feedback from the pretesting done in Phase 1. The focus of this application is for approval for Phase 1.

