## **2.0 Background / Literature Review / Rationale for the study:**

The U.S. Food and Drug Administration (FDA) announced in 2016 that it would begin redefining “healthy” food labels, in part spurred by a dispute with KIND Snacks about its use of the term on KIND Bar packaging. The lack of an updated regulatory definition of the term has left food companies like KIND vulnerable to class action and consumers vulnerable to confusing or misleading food labels. The FDA, however, has made no regulatory decisions since the initial 2016 request for information. In the interim, the FDA has held a public meeting on the redefinition, updated its Nutrition Innovation Strategy to include defining the term, and got approval from the Office of Management and Budget (OMB) to create a focus group review of a “healthy” icon on food packages. Most recently, OMB approved another proposal from the FDA to redefine the term and produce additional research on developing a “healthy” front-of-package (FOP) icon. However, no research evaluating the impact of a “healthy” label, particularly one endorsed by the FDA, currently exists in a U.S. population.

The influence of an FDA-endorsed “healthy” label on food choice is also presumed to interact with the level of trust participants have in food-related institutions like the FDA. Survey questions of attitude-based trust questions (e.g., “generally speaking, would you say that most people can be trusted or that you can’t be too careful in dealing with people?”) have shown varying relationships with choice.

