## Analysis Plan

### Statistical Models

We will run the following models to test our hypothesis.

- A binary logistic regression to assess the proportion of participants that choose healthy and unhealthy snack choices. The main predictor variable is the presence of an FDA Healthy, Healthy, or Food Compass Score. Other predictor variables to analyze are generalized trust, personal trust, institutional trust and trust in the government, knowledge, physical activity levels, diet, and sociodemographics.

We will run the same model for each treatment to test, for example, hypothesis H2.

- We plan to run a multinomial logit model (MNL), random parameter model (RPL), random parameter model with EC (RPL-EC), and latent class analysis (LCA) to investigate participants' willingness to pay on each treatment. We will use the presence of a healthy label or food compass score, and price as the main attributes of the utility function for the MNL, RPL, RPL-EC and LCA. However, for the LCA we will use generalized trust, personal trust, and trust in the government (according to hypothesis H2) as consumers' characteristics for the segment membership function.

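### The rationale presumes that trust modifies the effect of the FDA label, but no trust-by-label term or cross-treatment contrast of trust coefficients is specified

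*Combined protocol and SAP*

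**What the plan says.** Section 2.0 (Background) states that the influence of an FDA-endorsed healthy label "is also presumed to interact with the level of trust participants have in food-related institutions like the FDA". Objective 3 in section 1.0 concerns the label "both with and without FDA endorsement, on snack food choices". Objective 2 concerns the impact of trust in food-related institutions on food choice.

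Under Statistical Models, the logistic regression is described in two steps. First: "The main predictor variable is the presence of an FDA Healthy, Healthy, or Food Compass Score". Then: "Other predictor variables to analyze are generalized trust, personal trust, institutional trust and trust in the government", followed by knowledge, physical activity, diet and sociodemographics. The next line reads: "We will run the same model for each treatment to test, for example, hypothesis H2". The choice models (MNL, RPL, RPL-EC, LCA) are to be run "to investigate participants' willingness to pay on each treatment". Trust enters these only through the LCA segment membership function: "for the LCA we will use generalized trust, personal trust, and trust in the government". That list is marked as following hypothesis H2 and does not include institutional trust.

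Inference Criteria sets p < .05 and plans paired t-tests and ANOVA for before-and-after label differences, with the same tests for differences between treatments. Exploratory Analysis implies two trust questions: whether institutional trust predicts choosing a healthy snack carrying a Food Compass Score, and whether trust in the government predicts choosing an FDA-healthy snack.

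**The concern.** Two questions about trust need to be kept apart. One is prediction: do more trusting shoppers choose the healthy snack more often? The other is modification: does the label move trusting shoppers more than distrustful ones? Section 2.0 raises the second. The models as written estimate the first.

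If trusting shoppers choose healthier snacks whatever the label, a per-treatment trust coefficient will tend to be significant and could be reported as trust changing the response to the FDA label. If the trust coefficient is significant under one label and not another, that too could be read as a difference between labels, although no test of the difference has been made. Either reading would bear on the study's policy conclusion about FDA endorsement.

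**Working it through.** **Is there a figure to reproduce?** No. Section 5.2 justifies 350 to 400 participants by saturation and gives no effect size, event rate or power. The argument is therefore algebraic, and the numbers below are illustrations.

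**What each model identifies.** Let L = 1 for a labelled choice and T = trust, with

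logit P(healthy choice) = a + bL + cT + d(L × T).

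- The label effect at trust level T is b + dT. Modification means d ≠ 0.
- A model with L and T as separate predictors sets d = 0, so the label effect is b at every trust level.
- If a treatment contains labelled choices only, the slope on T is c + d. A significant slope cannot separate c from d.

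So whether or not a treatment's data include unlabelled choices, the stated model does not estimate d.

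**Illustration 1: a general trust effect with no modification (d = 0).** Assumed: 400 people, 8 choices each (4 labelled), ICC 0.2, participant-clustered errors, two-sided 0.05. The 400 and the 8 match the Phase 2 text in sections 5.2 and 6.0 (Data Exclusion says twelve scenarios). The 4/4 split, the ICC and the trust effects are assumptions. With 800 simulated datasets per setting:

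| Trust log-odds per SD (c) | Trust significant, labelled choices only |
|---|---|
| 0.15 | 57% |
| 0.20 | 78% |
| 0.30 | 99% |

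The interaction test rejected in 4% to 6% of datasets across the three settings. A second run of 500 datasets per setting gave 55%, 74% and 98%, with interaction rejections of 5% to 7%. In that run the additive label-plus-trust model, which is closer to the plan's wording, found trust significant in 69%, 89% and 99.8%.

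The high percentages are correct detections of a real trust effect. They become errors only if reported as evidence that trust changes the label's effect.

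**Illustration 2: comparing significance across separate fits.** Suppose the true trust effect is the same in two treatments and each fit has power p. Ignoring the wrong-direction tail, P(exactly one significant) = 2[p − P(both significant)], which is 2p(1 − p) when the estimates are independent.

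- p = 0.5: 2 × 0.5 × 0.5 = 50%
- p = 0.8: 2 × 0.8 × 0.2 = 32%

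Data Exclusion suggests that each participant answers scenarios in all three treatments, so the estimates may be correlated. At correlation 0.5 (bivariate normal) the figures are about 33% and 23%. A direct test of the difference would reject in 5%.

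**Price of the direct test.** Suppose trust acts in one treatment only and a single fit has 80% power, so the mean z is 1.960 + 0.842 = 2.802. Power of the difference test = Φ(2.802/√(2(1 − ρ)) − 1.960):

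- ρ = 0: Φ(1.981 − 1.960) = 51%
- ρ = 0.3: Φ(2.368 − 1.960) = 66%
- ρ = 0.5: Φ(2.802 − 1.960) = 80%

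**Do other parts of the plan fill the gap?** The t-tests and ANOVA in Inference Criteria compare treatments. As described they do not involve trust, and they name no outcome or contrast. The LCA membership function lets trust predict class and lets label preference differ by class. That is a link, but an indirect one; no test of it is stated, and institutional trust is not in it.

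**The case against.** The strongest reply is that the visible text points to prediction. Objective 2 asks about the impact of trust on food choice, and Exploratory Analysis asks whether an index predicts choosing a labelled snack. The wording of H2 is not in the text available for review. If H2 is a prediction hypothesis, the per-treatment model answers it. This stands, and it is why those models should be kept. It does not supply a test of the interaction presumed in section 2.0.

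Four stronger readings are tempting, and the documents do not support them:

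- **That labels are compared only by setting p-values from separate fits side by side.** Inference Criteria plans between-treatment tests, and the plan nowhere states a rule of comparing significance across fits. What can fairly be said is that those tests are loosely specified and suit repeated binary choices poorly.
- **That the plan has no link between trust and label response.** The LCA membership function provides one, indirectly.
- **That H2 will be wrongly declared supported.** This cannot be judged without its wording.
- **That leaving institutional trust out of the LCA is an error.** The list is tied to H2 and may be deliberate. Institutional trust is in the logistic model. It is also the index named for the Food Compass question, so an explanation is a reasonable request.

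It is also fair to object that the simulation inputs are not the plan's, and that the labelled-only fit is not exactly the stated model. The algebra does not depend on either.

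**Conclusion.** The concern holds as a gap in specification. The plan presumes that trust modifies the FDA label's effect, but its logistic and WTP models contain no trust-by-label term and no cross-treatment contrast of trust coefficients. The between-treatment tests and the LCA do not fill that gap. A per-treatment trust coefficient supports a statement about who chooses healthy snacks, not about whom the label influences.

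The size cannot be fixed from the documents. The 57% to 99% range rests on the assumed trust effects, ICC and labelled split. The 50% and 32% discordance figures assume independent estimates, fall to about 33% and 23% at correlation 0.5, and apply only if someone compares significance across fits, which the plan does not say it will do.

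**What to change.** 1. Keep the per-treatment logistic models, and state that they address whether trust predicts choosing the healthy snack.
2. Add one pooled choice-level model over all treatments, with participant-level clustering or random effects, label type (none, Healthy, FDA Healthy, Food Compass), the trust indices, and label × trust terms. The none level requires unlabelled choices; without them, take Healthy as the reference.
3. Name FDA Healthy × trust in the government and Food Compass × institutional trust as the tests of whether trust modifies the label effect.
4. Estimate FDA Healthy minus Healthy as a named contrast in this model and in a joint WTP model, in place of the t-tests and ANOVA on repeated binary choices.
5. Add institutional trust to the LCA membership function, or state why it is left out.

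The cost is analysis-plan wording and modelling work; no additional data items are needed. Interaction tests have less power than main-effect tests, so claims about trust will be more modest.

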### Phase 2 – Full Collection

The second phase of this study involves full collection of the experiment using our survey on Qualtrics in the Winter / Spring of 2023. A table will be set up for willing market shoppers to stop and take the survey on iPads provided by Tufts. The survey is expected to take 15-20 minutes to complete.

As part of the choice experiment section, participants will be presented with choices between two to three snack food products and accompanying renderings of food labels for each product. Participants select only one product on each choice scenario (they will be exposed to 8 choice scenarios). Alternatively, if participants don't want to choose any of the snack products, they can opt out by choosing the "no purchase" option. After they finish making their nine choices, they will randomly pick a number to select one of the nine choice scenarios as the binding choice scenario. Participants will only pay for the (one) snack product they chose in the binding choice scenario. If the participant selected the "no purchase" option in the selected binding choice scenario, they won't receive a product and won't have to pay anything. The research team will have the snack products readily available so participants can have their product as soon as they pay for it.

Since the Real Choice Experiment mandates that the selection is binding and that the subject will pay for their chosen product, the research team will give participants \$5 cash at the beginning of the study after they signed the consent form and answer the screening questions. The screening questions are if participants are 18 years or older and if they are responsible for shopping for food for the household.

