### Transformations

We will use simple coding for the following categorical variables:

- Income
- Education
- Race

The variable "Diet" will be a dummy variable that takes the value of 0 if participants responded no / not applicable, and the value of 1 if any of the other options is selected.

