### Data Exclusion

We will verify that each participant answered each of the twelve choice scenarios for the three treatments. Straightlining: If found that participant will be excluded from the survey. Outliers will be included in the analysis.

47  
48 **Missing Data**  
49

50 If a participant doesn't answer any of the twelve choice scenarios, and / or answer the trust-related  
51 questions, that participant will not be included in the analysis.  
52

53 **Exploratory Analysis**  
54

55 If the institutional trust index doesn't predict the probability of choosing a healthy snack labeled with a  
56 Food Compass Score, we will explore the effect of interpersonal trust or generalized trust in the logistic  
57 regression.  
58

59 If the index measuring trust in the government doesn't predict the probability of choosing an FDA-  
60 healthy snack, we will explore the effect of interpersonal trust or institutional trust in the logistic  
61 regression.

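### The willingness-to-pay models enter the Food Compass Score only as present or absent; if products show differing scores, the result cannot be compared with the 'Healthy' and 'FDA Healthy' figures

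*Combined protocol and SAP*

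**What the plan says.** The combined protocol and SAP plans two kinds of model under Analysis Plan, Statistical Models.

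- **Logistic model.** The outcome is the type of snack chosen: "A binary logistic regression to assess the proportion of participants that choose healthy and unhealthy snack choices". The label enters as an indicator: "The main predictor variable is the presence of an FDA Healthy, Healthy, or Food Compass Score".
- **Choice models (MNL, RPL, RPL-EC, LCA).** Their purpose is "to investigate participants' willingness to pay on each treatment". For the utility: "We will use the presence of a healthy label or food compass score, and price as the main attributes of the utility function".

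Under Transformations, the sentence "We will use simple coding for the following categorical variables" introduces income, education and race, and a dummy for diet follows. No coding is given for the Food Compass Score.

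On what shoppers see, section 6.0 (Phase 2) says that "participants will be presented with choices between two to three snack food products and accompanying renderings of food labels for each product". It does not name the Food Compass Score. The one remark on placement is under Exploratory Analysis, "If the institutional trust index doesn't predict the probability of choosing a healthy snack labeled with a" Food Compass Score, which does not say whether unhealthy snacks also carry one. The scale and the displayed values appear nowhere.

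Objective 4 in section 1.0 is to find the label components best suited to policy that would make snack choices healthier.

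**The concern.** 'Healthy' and 'FDA Healthy' are claims that point one way, so present/absent coding suits them. A score takes values: a high one may attract a health-minded shopper and a low one may deter the same shopper. If both are on the table, an indicator that a score is shown takes the same value for the attractive and the unattractive product. What the label tells the shopper then never enters the utility.

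At stake is the comparison of WTP across the three labels. A score that steers choice strongly could show a WTP near zero beside the two claims. The logistic model could meanwhile report a clear shift toward healthy snacks. The study would then hold two results that appear to conflict, with no planned way to reconcile them.

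**Working it through.** The documents give no WTP, score range or design matrix, so there is no stated figure to reproduce. Every number below is an illustration on assumed inputs.

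**1. What presence coding estimates when both products are scored.** Assume two products scored 70 and 30 plus no purchase, equal baseline liking, a price coefficient of -0.8 per dollar, utility rising by s per 10 points, and a neutral score of 50. The label then adds +2s to one product and -2s to the other.

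- WTP for 70 over 30: 4s / 0.8.
- Presence coefficient at equal prices, from matching the overall propensity to buy: d = ln[(e^(2s) + e^(-2s)) / 2]. Presence WTP = d / 0.8.
- For s = 0.25: 4 × 0.25 / 0.8 = $1.25. d = ln[(1.6487 + 0.6065) / 2] = ln 1.1276 = 0.120, and 0.120 / 0.8 = $0.15.

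A simulation of 200,000 choice sets, with prices of $1.50 to $4.50 and the score shown in half, gave:

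| s per 10 points | True WTP, 70 over 30 | Presence WTP, by hand | Presence WTP, simulated | Score-coded WTP, simulated |
|---|---|---|---|---|
| 0.10 | $0.50 | $0.02 | $0.01 | $0.51 |
| 0.25 | $1.25 | $0.15 | $0.12 | $1.23 |
| 0.40 | $2.00 | $0.36 | $0.28 | $2.00 |

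**2. The small presence figure depends on the neutral score.** Keep s = 0.25, so that the gap is still worth $1.25.

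- Neutral at 30 (label effects +1 and 0): ln[(2.7183 + 1) / 2] / 0.8 = 0.620 / 0.8 = $0.78.
- Neutral at 70 (0 and -1): ln[(1 + 0.3679) / 2] / 0.8 = -0.380 / 0.8 = -$0.47.

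So one and the same gap of $1.25 is compatible with presence WTPs from -$0.47 to $0.78. The presence figure does not reveal the gap.

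**3. How the label layout matters.** A second illustration used 400 people × 8 scenarios, price coefficient -1, and label effects worth +$0.50 (high score) and -$0.50 (low score), with one simulated data set per layout. The score-coded column is per score step (true $0.50).

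| Layout | Presence WTP | Score-coded WTP |
|---|---|---|
| Both products scored, pooled with unlabelled scenarios | $0.09 | $0.54 |
| Score shown or not, independently by product | -$0.06 | $0.48 |
| Only the healthy product scored | $0.39 | $0.39 |
| Every product scored, fitted within that treatment | not identified | $0.58 |

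In the last row presence is 1 for every product and 0 for no purchase, which is exactly the buy/no-purchase constant. Only the sum of the two coefficients can be estimated (information matrix of rank 2 for 3 parameters).

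**4. The logistic model.** In the first layout of step 3 the healthy share among buyers rose from 49.6% to 67.9%. In the s = 0.25 case of step 1 it rose from 50% to 69%. A presence indicator against a healthy/unhealthy outcome picks up that shift.

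**5. Whether score coding alone suffices.** In the s = 0.25 setting, with the score and a scores-shown indicator but no product constants, the estimate of the $1.25 gap becomes $0.23 if the healthy snack starts $1.00 less liked, and $1.76 if it starts $0.50 more liked. With product constants it is $1.25 to $1.26.

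**The case against.** The strongest reply is that the premise is not in the documents. A reader might infer from section 6.0 that every product shows a graded score. The text says only that label renderings accompany the products, and the Exploratory Analysis wording is compatible with scores on healthy snacks alone. In that layout presence and score coding coincide. This stands, and makes the point conditional. It does not remove it, because the plan does not say which layout applies, and presence coding averages out or fails in the other three layouts tried.

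A reader might also infer that the plan cannot detect a move toward higher-scored snacks. That goes too far. The logistic outcome is healthy versus unhealthy choice, and Inference Criteria adds before/after and between-treatment tests. These put all three labels on one outcome and can show the shift, provided that the healthy snacks are the higher-scored ones. The logistic model can keep its presence indicator.

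Lastly, the utility sentence could be parsed as the presence of a healthy label, or else the score itself, and it speaks of main attributes, not of all attributes. The parallel logistic sentence makes presence the natural reading, and no section supplies a score term. The ambiguity is itself a reason to rewrite the sentence.

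**Conclusion.** The point holds for the four choice models, conditionally. As written, they have no term for the score's value, so they cannot give WTP for a higher over a lower score. If products show differing scores, the presence WTP is an average over high and low scores. If every product is scored and the model is fitted within that treatment, it is not identified. Either way it is not on the same footing as the WTP for 'Healthy' and 'FDA Healthy'. In the illustration it is $0.12 where the gap is worth $1.25.

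It would be wrong to call the Food Compass WTP meaningless outright: if only healthy snacks carry a score, it is interpretable once product constants separate baseline taste. The dollar figures rest on assumed scores, baseline tastes, neutral score and price coefficient. The direction of the problem rests only on products showing differing scores, which the sponsor can confirm or rule out from the label renderings.

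**What to change.** In Analysis Plan, Statistical Models:

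1. State which products show a Food Compass Score, and the value on each.
2. Where values differ, replace presence in the MNL, RPL, RPL-EC and LCA utilities with the displayed score of each alternative: per 10 points, or as high/low levels if few values are used, and zero where none is shown. Add a scores-shown indicator and product-specific constants.
3. Fit this on labelled and unlabelled scenarios together. If each product always shows the same score, its constant and its score cannot be separated within labelled scenarios alone.
4. Report WTP for the actual score gap between the study products, and use that figure beside the WTP for 'Healthy' and 'FDA Healthy'.
5. Keep presence coding for those two labels and for the logistic model. If only healthy snacks carry a score, say so, keep presence coding there too, and add product constants.

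The cost is SAP wording, one recoded column and a few extra parameters. The continuous form also assumes linearity across the displayed scores, which the high/low form avoids. No new data are needed.
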